### Plans to promote participant retention and complete follow-up {18b}

Participants will be contacted multiple times by text, email, or phone to gather follow-up data and maintain engagements. If participants are lost to follow-up, the hospital medical record system will be used to assess for HRDwC. However, if none are found, or there is no data regarding further care, they will be considered lost to follow-up (LTFU).

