**Fig. 3 Fig3:**
[figure not shown]
Adaptive design: interim analyses

Recruitment will be considered feasible if > 3 participants are enrolled per month and the follow-up rate is at least 70%. Acceptability will be measured by a 7-point Likert scale, and the acceptability goal will be having > 50% of clinicians reporting the decision aid to be somewhat or extremely helpful. Regarding fidelity, a 3rd party will rate conversations on pre-defined criteria for SDM (OPTION-5 scale: *observing patient involvement*) [25]. If > 50% of intervention group conversations and < 30% of usual care conversations are rated as utilizing SDM, this condition will be considered satisfied. If two of three initial goals are not met (recruitment, acceptability, and fidelity), we will pause the trial and implement appropriate changes to the protocol.

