#### Outcome measures: efficacy

We selected outcome measures via input from the Steering Committee, patients, and practicing clinicians as well as previous literature [26]. We also have included in the post-enrollment survey a measure assessing outcome priorities in the studied population. As stakeholders generally represent two different groups (patients and clinicians), we considered two outcomes as primary [27]. Clinicians endorsed radiation exposure as the most important primary outcome, measured as the proportion of patients receiving a CT scan during the ED visit and within 60 days and total radiation exposure in 60 days. Patients endorsed knowledge as a primary outcome, and the steering committee created and piloted a 10 question knowledge test.

We also selected a number of secondary outcomes based on stakeholder input. Secondary efficacy outcomes include 1 - clinician effort to engage patients in SDM (OPTION-5 scale), 2 - patient engagement as measured by CollaboRATE and SDM question(s), 3 - patient satisfaction (items from the Hospital Consumer Assessment of Healthcare Providers and Systems [HCAHPS]), 4 - trust in physician (trust in physician scale, 5 questions) and several implementation outcomes regarding the helpfulness of the intervention (see post-encounter patient and clinician data collection forms, Supplementary Materials 3 and 4) [25, 28, 29].

Safety outcomes include the primary outcome of radiation exposure (number of CT scans obtained on day 0 and within 60 days), total radiation in 30 days/60 days (milli-gray [mGy]) from diagnostic imaging, and the incidence of high-risk diagnoses with complications (HRDwC) that could be related to missed or delayed diagnoses. These HRDwC have been previously defined [10].

Operational outcomes will include (1) ED revisits (in 7/30/60 days) and hospital admissions on second visit, (2) ED length of stay (LOS) (minutes), (3) admission rate, (4) final diagnosis for initial visit, (5) 60-day alternative diagnoses, and (6) urologic procedures (in 30/60 days).

Implementation outcomes will include (1) clinicians’ ratings of conversation/decision aid (“would you recommend,” “would you use again,” and qualitative feedback), (2) acceptability (clinicians’ ratings, qualitative and quantitative), and (3) Fidelity (RA checkboxes) as well as adherence to protocol.

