### Sample size {14}

As per Fig. 3, three discrete analysis times are planned.

Our sample size for phase I (until interim analysis 1) is based on the expert recommendation that at least 50 subjects be included to examine the pragmatics of recruitment [30].

For the endpoint of reduction in the use of CT scans, assuming a base proportion of 80% (currently, the usage rate for kidney stones), a sample of 200 patients (100 patients per group) will provide 87% power to detect a reduction of CT use to 60%, as significant at a *p* value of 0.047 (adjusted to account for the interim efficacy analysis—see explanation below). A final sample size of 200 is large enough to account for a loss of 10% and still provides about 80% power to detect the hypothesized difference. If lost to follow-up rates are higher, a sample size of 250 will be used (125 patients per group).

For the endpoint of knowledge, we hypothesize that an improvement of 2 points (of 10) is clinically significant. If the decision aid improves knowledge from 6/10 to 8/10, we will be powered at 0.80 to detect this with a total of 70 participants.

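### An unreachable patient counts as followed up for HRDwC only if the hospital record shows one, so the incidence has an outcome-dependent denominator if lost patients are dropped

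*Protocol article*

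**What the plan says.** Protocol article, Plans to promote participant retention and complete follow-up {18b}: "If participants are lost to follow-up, the hospital medical record system will be used to assess for HRDwC". The next sentence reads: "However, if none are found, or there is no data regarding further care, they will be considered lost to follow-up (LTFU".

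The two conditions in that sentence are joined by *or*, so unreachable patients fall into three groups:

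- The record shows an HRDwC: status known, event counted.
- The record shows later care but no HRDwC: lost to follow-up.
- The record shows nothing further: lost to follow-up.

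The section Outcome measures: efficacy lists among the safety outcomes "the incidence of high-risk diagnoses with complications (HRDwC) that could be related to missed or delayed diagnoses". The other safety outcomes listed there are radiation measures.

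On the amount of loss, Sample size {14} says "A final sample size of 200 is large enough to account for a loss of 10" per cent. The feasibility criteria below Fig. 3 require that "the follow-up rate is at least 70" per cent.

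No section sets a denominator for HRDwC. The intention-to-treat statement under Multivariable analyses concerns the primary analyses. Section {20c} says only that missing data will be described and, if extensive, discussed as a limitation. Section {18a} has events confirmed by chart review, but does not say how an unreachable patient with a clean chart is counted.

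**The concern.** Two unreachable patients undergo the same record search, and the result alone decides whether they count as followed up. Among unreachable patients, only those with the event have a known outcome. An incidence needs a denominator. If the lost patients are removed from it, the search adds events to the numerator without adding the event-free patients it also found.

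HRDwC is the listed safety outcome directed at missed or delayed diagnosis, which is the plausible harm of an intervention meant to reduce CT use. A rate whose denominator depends on the outcome is hard to interpret within an arm. If the arms lose different proportions of patients, the comparison between them is affected as well.

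**Working it through.** **Plan's own figure.** The documents state no HRDwC rate, so the only nearby figure to reproduce is the power for CT use: "a sample of 200 patients (100 patients per group) will provide 87% power" for 80% against 60% at a two-sided level of 0.047. With pooled variance, z = 1.986 and the null standard error is √(2 × 0.7 × 0.3 / 100) = 0.0648. Power is Φ[(0.20 − 1.986 × 0.0648) / √((0.16 + 0.24) / 100)] = Φ(1.127) = 0.870, which agrees. With 90 per group it is 0.833 (0.788 with continuity correction), consistent with the stated value of about 80%. The sample size is not in question. It supplies the planned loss of 10%.

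**Inputs.** Loss d is 10% (Sample size {14}) or 30% (the complement of the 70% feasibility floor). The following are assumptions, because the documents give none: risk p in reached patients, risk q in unreachable patients, and capture c, the share of unreachable patients' events that the hospital record shows.

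**Formulas.**

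- Rate under {18b}, lost patients removed: [(1 − d)p + d·c·q] / [(1 − d) + d·c·q].
- True rate: (1 − d)p + d·q.
- Same events over all randomised patients: (1 − d)p + d·c·q.

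**Equal risk, p = q = 1% (true rate 1.00%).**

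| Loss d | Capture c | Rate under {18b} | Over all randomised |
|---|---|---|---|
| 10% | 0.8 | 0.0098 / 0.9008 = 1.09% | 0.98% |
| 10% | 1.0 | 0.0100 / 0.9010 = 1.11% | 1.00% |
| 30% | 0.8 | 0.0094 / 0.7024 = 1.34% | 0.94% |
| 30% | 1.0 | 0.0100 / 0.7030 = 1.42% | 1.00% |

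At half capture the rule gives 1.05% and 1.21% at 10% and 30% loss. With no capture it gives 1.00%. The inflation factor hardly depends on the risk: at 30% loss and full capture it is 1.43 for p = 0.2% and 1.40 for p = 5%.

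**In counts.** Take 100 patients in an arm, 30 unreachable, one HRDwC among the 70 reached and one found in a record. The rule gives 2/71 = 2.8%. With everyone kept it is 2/100 = 2.0%.

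**When the direction reverses.** Let q = 5%, p = 1%, d = 30%. The true rate is 0.7 × 1% + 0.3 × 5% = 2.20%. At half capture the rule gives 0.0145 / 0.7075 = 2.05%, a factor of 0.93. With no capture it gives 1.00%, a factor of 0.45.

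**Between arms, equal true risk of 1%.**

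- Equal loss in both arms: ratio 1.00.
- Loss of 15% against 30%, capture 0.8: 1.14% against 1.34%, ratio 1.17.
- Loss of 10% against 30%: ratio 1.15 at half capture, 1.28 at full capture.

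**The case against.** **The denominator is inferred.** Section {18b} only labels patients, under a retention heading. It does not say that they leave the HRDwC analysis, and an analysis plan not shown here could keep them. This stands, and the point is therefore conditional. What does not depend on that plan is the label itself, which the protocol fixes by the search result.

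**The rule is cautious.** A clean chart at one hospital does not show that a patient was event-free. Section {18a} expects care elsewhere and seeks authorisation for outside records. Refusing to count chart-negative patients as event-free, while never discarding a known harm, is defensible in intent. But caution would treat both search results alike and show the uncertainty by bounds. It does not justify keeping only the positives.

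**The effect may be small.** At the planned loss, the assumed 1% rate moves by about 0.1 percentage point, with roughly one expected event per arm of 100. The 70% figure is a feasibility threshold checked after 50 participants, not the planned loss. Participants are blinded and the follow-up assessor does not know the arm, so unequal loss is less likely. The pause rule in {21a} counts related serious adverse events, not an HRDwC rate. All of this stands and lowers the grade.

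**Stronger readings a reader might infer.**

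- That the HRDwC rate is necessarily inflated. This needs similar risk in unreachable patients and fair chart capture, and the documents establish neither.
- That HRDwC is the trial's main safety rate. The protocol does not call it that. It also collects 60-day alternative diagnoses, ED revisits, admissions and deaths.
- That the rule raises the loss count that moves the target to 250 patients. Compared with a definition based on contact alone, the rule lowers that count, because it rescues chart-positive patients. It raises the count only compared with a definition that also accepts clean charts.

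**Conclusion.** The point holds in conditional form and should be fixed; it does not threaten the trial's primary conclusions. As written, {18b} makes follow-up status for HRDwC depend on having an HRDwC, and no other section repairs this. If lost patients leave the denominator, an assumed 1% rate would be reported as 1.09 to 1.11% at the planned 10% loss and 1.34 to 1.42% at 30% loss. These figures assume equal risk in unreachable patients and 80 to 100% chart capture. With much higher risk and care elsewhere the rate can be too low instead. With equal loss in the two arms the risk ratio is essentially unchanged. A loss of 15% against 30% would make equal risks appear as a ratio of about 1.17 at 80% capture.

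**What to change.** Reword {18b} so that classification does not depend on what the search finds:

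1. Search the hospital record to day 60 for every unreachable patient, and record separately whether there is any later information and whether there is an HRDwC.
2. Report HRDwC over all randomised eligible patients in each arm, keeping chart-negative and no-data patients in the denominator.
3. Add a sensitivity analysis restricted to patients actually contacted, with chart-only events left out of the numerator as well.
4. Add best-case and worst-case bounds for patients with no later information.

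It is not enough to class as lost only those with no later record. Patients with an event generate records, so that rule would still depend partly on the outcome. The all-randomised denominator with bounds has to carry the analysis.

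Cost: a reworded rule and one table; the record search is already planned. Downside: events treated outside the hospital system may be missed in chart-only patients, so the all-randomised rate can be somewhat low (0.94% against a true 1.00% at 30% loss and 80% capture in the example). The bounds show this, though the worst case can be wide: 10 patients without information in an arm of 100 add up to 10 percentage points.

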### Data management {19}

All data collected will be stored using REDCap (Research Electronic Data Capture) hosted by the Tufts Clinical and Translational Science Institute. Electronic capture data point fields will include range limits to protect against accidental entry of impossible data points. Direct data entry at the time of collection will be utilized when possible, but paper forms will be available in the event of connectivity issues. Paper forms will be managed via standard operating procedures, they will be transported directly to research offices after use and stored in locked cabinets prior to data entry. Data entry will occur as close to data acquisition as logistically possible. Data management will be performed by trained research staff under the supervision of the PI. The PI will not have access to the randomization dataset while the trial is ongoing, other than at pre-specified points.

### Confidentiality {27}

All data collected during the course of the study will be kept strictly confidential and will only be accessed by members of the study team as required by study procedures, or by members of the overseeing IRB or other legally authorized parties. All physical documents will be stored in locked cabinets in locked offices of research staff. All electronic data will be housed in RedCap. Email and text messages will be sent from hospital email accounts and HIPAA compliant apps. Anonymized trial data will be available via the PI once the study is complete.

### Plans for collection, laboratory evaluation, and storage of biological specimens for genetic or molecular analysis in this trial/future use {33}

There will be no collection of biological specimens for future use.

## Statistical methods

### Statistical methods for primary and secondary outcomes {20a}

For the primary outcome, the univariable comparison of study groups on the proportion of CTs obtained will be conducted using Pearson’s chi-square. Univariable comparisons of study groups on questionnaire outcomes (e.g., patient knowledge, patients satisfaction) will be conducted with independent sample t-tests.

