### Eligibility criteria {10}

Eligible patients will include adults age 18–55 presenting to the ED with a chief complaint of flank pain who are being considered by the treating clinician for a CT scan for the diagnosis of ureterolithiasis. Exclusion criteria are listed in Fig. 2. Data will be collected on all patients assessed for eligibility and we will report the number of excluded patients, the rationale for each exclusion, and the number of patients who decline consent to participate in the study in accordance with the CONSORT guidelines for reporting randomized trials [23]. Participants with and without a history of ureterolithiasis will be eligible, but the intervention will be tailored to their history. Eligibility criteria were determined by stakeholder engagement during the process of decision aid development [20].

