## Assignment of interventions: allocation

### Sequence generation {16a}

#### Randomization

Patients will then be randomized via permuted blocked randomization [31, 32]. Randomization will be stratified by “history of stones” with separate randomization for subjects with a history of kidney stones, as the decision aid for these patients is different, because guidelines suggest avoiding CT for young healthy patients with a history of kidney stones [33]. Allocation will be based on a 1:1 ratio between the intervention and usual care arms. Though we will not be able to blind clinicians to use of the decision aid, patients will not be aware of whether they are receiving usual care or the decision aid, as the consenting information will refer to paper-based information—which accurately describes both the decision aid and the usual care information packet. The research staff will maintain a database recording randomization, which will be separate from general subject-level data and will not be accessible to the PI or statisticians until planned interim analyses.

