#### Multivariable analyses

We will apply ICH-E9 guidelines for statistical analysis and the CONSORT statement for reporting of findings for clinical trials [31, 34]. For multivariable analyses, linear regression or logistic regression will be used to adjust for baseline characteristics that do not appear to be balanced upon inspection or show moderate to large standardized effect sizes. Covariates that do not meaningfully modify estimates of treatment effect or otherwise contribute to clinical interpretation may be removed from the final model.

In multivariable models, we will assess for heterogeneity of treatment effects by including interaction terms (specifically, age, gender, and race/ethnicity, insurance, education, and health literacy) with treatment group [35]. In view of our limited sample size to detect significant interaction terms, we will consider any interaction term as worthy of further evaluation if significance testing achieves a critical test level of 0.15.

Our primary analyses will proceed via an intention-to-treat approach, as some cross-over is expected. All measures of treatment effects (e.g., odds ratios, difference in means or proportions) as well as estimates of group specific effects (e.g., means and proportions) will be reported with 95% confidence intervals. However, patients with exclusion criteria that manifest post-randomization will NOT be included (ex. pregnancy diagnosed in the ED).

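### The primary tests and the interaction list leave out stone history, the randomisation stratifier, and the adjusted models choose covariates from the data; the primary tests stay valid but can be conservative

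*Protocol article*

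**What the plan says.** **Design.** The Randomization text under Sequence generation {16a} stratifies by stone history, "with separate randomization for subjects with a history of kidney stones, as the decision aid for these patients is different", and adds that "guidelines suggest avoiding CT for young healthy patients with a history of kidney stones". Eligibility criteria {10} says: "Participants with and without a history of ureterolithiasis will be eligible, but the intervention will be tailored to their history".

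**Primary tests.** Statistical methods {20a} states that the "univariable comparison of study groups on the proportion of CTs obtained will be conducted using" Pearson's chi-square. Questionnaire outcomes, including knowledge, get independent-sample t-tests. Neither uses the stratum.

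**Adjusted models.** The Multivariable analyses text uses regression to "adjust for baseline characteristics that do not appear to be balanced upon inspection or show moderate to large standardized effect sizes". It continues: "Covariates that do not meaningfully modify estimates of treatment effect or otherwise contribute to clinical interpretation may be removed". Section {20c} repeats that baseline imbalance informs the model.

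**Interactions.** The same text lists the terms to be crossed with treatment: "specifically, age, gender, and race/ethnicity, insurance, education, and health literacy". Each is flagged at a test level of 0.15. Stone history is not on the list.

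**Related text in Interim analyses {21b}.** The second interim may lead to exclusion of patients with a stone history. The section also promises stratified analyses for baseline covariates known to be strongly related to outcome, or imbalanced on inspection. It names none and does not connect them to the primary test.

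**The concern.** By the protocol's own reasoning, stone history may bear on CT use and it decides which version of the decision aid a patient receives. Three choices sit badly with that.

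1. Stratified randomisation removes between-stratum variation from the comparison of arms. An unstratified test still counts that variation in its standard error, so the standard error is too large whenever the outcome differs by stratum. The cost is precision.
2. A covariate that enters because it looks imbalanced, and stays because it moves the treatment estimate, is chosen partly on the result. No thresholds are given and removal is discretionary, so the adjusted estimate depends on decisions made after seeing data. The design forces balance on stone history, so an imbalance rule will tend not to pick it. Other prognostic but balanced covariates can be passed over in the same way.
3. The one baseline factor by which the intervention itself differs, and on which the trial may later restrict entry, has no named interaction with treatment.

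**Working it through.** **Inputs from the protocol.** Sample size {14}: control CT use 80%, intervention 60%, 100 per arm, final level 0.047. Interim analyses {21b}: two-sided test. Randomization: 1:1 within strata.

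**Inputs assumed.** The protocol gives neither the share with a stone history nor CT rates by stratum. I take equal strata (50 per arm per stratum), control CT use averaging 80%, and a 20-point reduction in each stratum. The gap in CT rate between strata varies from 0 to 30 points.

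**Step 1: the plan's own power figure.** Two-sided 0.047 gives z = 1.986. With pooled variance under the null:

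- SE under null = √(2 × 0.70 × 0.30 / 100) = 0.0648
- SE under alternative = √((0.80 × 0.20 + 0.60 × 0.40) / 100) = 0.0632
- Power = Φ((0.20 − 1.986 × 0.0648) / 0.0632) = Φ(1.127) = 0.870

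The stated 87% reproduces.

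**Step 2: true size of the unstratified chi-square.** The test uses variance 0.80 × 0.20 = 0.16 per patient. The variance that actually applies is the average within strata. True size is therefore about 2 × [1 − Φ(1.986 / √(within-stratum variance / 0.16))].

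- 90%/70%: (0.09 + 0.21)/2 = 0.150; ratio 0.9375; effective z = 1.986/0.968 = 2.051; size about 0.040
- 95%/65%: (0.0475 + 0.2275)/2 = 0.1375; ratio 0.859; effective z = 1.986/0.927 = 2.143; size about 0.032

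**Step 3: simulation** (200,000 replicates, chi-square against Cochran-Mantel-Haenszel, CMH).

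| Stratum CT rates | Gap | Size, chi-square | Size, CMH | Power, chi-square | Power, CMH |
|---|---|---|---|---|---|
| 80/80 | 0 | 0.048 | 0.047 | 0.875 | 0.874 |
| 85/75 | 10 | 0.046 | 0.047 | 0.874 | 0.876 |
| 90/70 | 20 | 0.041 | 0.047 | 0.880 | 0.889 |
| 95/65 | 30 | 0.033 | 0.047 | 0.890 | 0.911 |

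With 30% rather than 50% having a stone history, the pattern is the same: at gaps of 20 and 30, size is 0.042 and 0.036, and power goes from 0.880 to 0.887 and from 0.887 to 0.904. For a smaller 15-point effect with equal strata, power goes from 0.663 to 0.663 (gap 10), 0.663 to 0.679 (gap 20) and 0.671 to 0.713 (gap 30).

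**Step 4: the t-test for knowledge.** With an assumed within-stratum SD of 2.5 and equal strata, its level falls from 0.047 with no stratum difference to 0.032 at a 2-point difference and 0.021–0.022 at 3 points.

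**Step 5: covariate selection.** A linear model was simulated with 200 patients, six covariates and no treatment effect. Assumptions: entry at a standardised difference above 0.2, retention if the estimate changes by more than 10%, and covariate–outcome correlation 0.2 or 0.35. At nominal 0.047:

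| Model | Level, correlation 0.2 | Level, correlation 0.35 |
|---|---|---|
| Selected by the two rules | 0.038 | 0.015 |
| All six fixed in advance | 0.048 | 0.043 |
| Most favourable of unadjusted and selected | 0.056 | 0.051 |

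**Step 6: the listed interactions.** Six tests at 0.15 give 1 − 0.85⁶ = 0.62 as the chance of at least one false signal if independent. None of the six concerns stone history.

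**The case against.** **The primary test is valid.** This stands. Ignoring the stratifier can only make it conservative. A reader might infer a false-positive risk or a wrong power figure; the calculations show neither, and 87% is met in every scenario.

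**The loss is small and rests on assumption.** This also stands. That guidelines discourage CT in some patients with prior stones does not establish what clinicians at this site do. Entry requires that the clinician is already considering CT, which may narrow any gap. At gaps up to 10 points, stratifying gains next to nothing.

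**The effect by stone history may still be seen.** A reader might infer from the interaction list that it will never be examined. The text does not support that: the stratified analyses promised in {21b} could take in stone history. They do not name it, however, and they leave the primary test and the interaction list unchanged.

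**The adjusted models are secondary, and the removal rule is permissive.** They follow a fixed univariable test, and a covariate can also be kept for clinical interpretation. A reader might infer that the adjusted intervals are too narrow. In the simulation the selected model was conservative, and choosing the most favourable model raised the level only slightly. What remains is that the adjusted estimate depends on the data through rules without thresholds.

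**Covariate detail belongs in an analysis plan.** In general yes, and none is shown here. But this article itself fixes the tests, the selection rule and the interaction list, so the point concerns what it states.

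**Conclusion.** The point holds as one of efficiency and pre-specification. It does not threaten the validity of the primary result.

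- **Primary tests:** valid, and conservative if the outcome differs by stone history. At the planned effect with equal strata, stratifying is worth about 0 points of CT power at gaps of 0 to 10, about 1 at 20 and about 2 at 30. These gaps are assumptions, since the protocol gives no rates by stratum. This is the weakest of the three parts.
- **Adjusted models:** the entry and removal rules make the adjusted estimate data-dependent and tend to miss the stratifier. This is the strongest part.
- **Interactions:** stone history is absent although the intervention differs by it and the second interim may exclude patients on it. The general promise of stratified analyses does not fill that gap.

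The change should be made, since with no stratum difference it costs essentially nothing (power 0.875 against 0.874).

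**What to change.** 1. Make the primary CT analysis a Cochran-Mantel-Haenszel test stratified by stone history, with a stratified risk difference and its confidence interval.
2. Analyse knowledge by linear regression on arm and stone history.
3. Replace the imbalance and change-in-estimate rules with a covariate list fixed in advance on prognostic grounds. Which covariates join stone history is for the trial team to decide; education and health literacy, already on the interaction list, are natural candidates for knowledge.
4. Add arm by stone history to the pre-specified interactions. Report the effect within each stratum, and read it as exploratory because the protocol itself acknowledges that the sample is limited for interactions.
5. In {21b}, name stone history in the stratified analyses and say how they relate to the primary test.

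The cost is wording only. Stone history must be known at randomisation, so no new data or patients are needed. The change is best made before the second interim, when efficacy is first assessed and restriction by stone history may be considered.
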